## Abstract

**Background:**

Checkpoint inhibitors (CPIs) are widely used in cancer treatment, with transformative impacts on survival. They nonetheless carry a significant risk of toxicity in the form of immune-related adverse events (IrAEs), which may be sustained and life-altering. IrAEs may require high-dose and/or prolonged steroid use and represent a significant healthcare burden. They mimic immune-mediated inflammatory diseases (IMIDs) but understanding of their pathogenesis is limited. The MEDALLION project aims to determine targetable mechanisms of immune dysregulation in IrAE development, employing an immune monitoring approach to determine changes in circulating and tissue resident cells of CPI recipients who do/do not develop them and assessing the contribution of the microbiome in parallel.

**Methods:**

MEDALLION is a non-randomised longitudinal cohort study aiming to recruit 66 cancer patient recipients of anti-PD1/PD-L1, anti-CTLA-4 or combination therapy. Eligible participants include those with malignant melanoma in the adjuvant or metastatic setting, mesothelioma and non-small cell lung carcinoma (NSCLC) treated in the metastatic setting. Comprehensive clinical evaluation is carried out alongside blood, skin swab and stool sampling at the time of CPI initiation (baseline) and during subsequent routine hospital visits on 6 occasions over a 10-month follow-up period. It is conservatively anticipated that one third of enrolled patients will experience a “significant IrAE” (SirAE), defined according to pre-determined criteria specific to the affected tissue/organ system. Those developing such toxicity may optionally undergo a biopsy of affected tissue where appropriate, otherwise being managed according to standard of care. Peripheral blood mononuclear cells will be analysed using multi-parameter flow cytometry to investigate immune subsets, their activation status and cytokine profiles. Stool samples and skin swabs will undergo DNA extraction for 16 S ribosomal RNA (rRNA) sequencing and internal transcribed spacer (ITS) gene sequencing to determine bacterial and fungal microbiome diversity, respectively, including species associated with toxicity. Stored tissue biopsies will be available for in situ and single-cell transcriptomic evaluation. Analysis will focus on the identification of biological predictors and precursors of SirAEs.

**Discussion:**

The pathogenesis of IrAEs will be assessed through the MEDALLION cohort, with the potential to develop tools for their prediction and/or strategies for targeted prevention or treatment.

**Trial Registration:**

The study was registered on 18/09/2023 in the ISRCTN registry (43,419,676).

## Background

Checkpoint inhibitors (CPIs), including anti-programmed cell death protein 1/programmed death-ligand 1 (PD1/PD-L1) and anti-cytotoxic T-lymphocyte-associated protein 4 (CTLA-4) monoclonal antibodies, are now widely used across multiple cancer subtypes in the setting of metastatic, adjuvant and neoadjuvant indications [1]. Indeed, since the US Food and Drug Administration (FDA) approved the first CPI immunotherapy, the realisation of durable responses in subsets of patients across a range of poor-prognosis malignancies has proved transformative. This has come with the unfortunate cost of immune-related adverse events (IrAEs) in many recipients, however. Those of a “severe” nature (grade 3 or above according to common terminology criteria for adverse events, CTCAE) [2], occur in around 55% of people treated with anti-PD1/CTLA-4 combination therapy [3], including colitis (20%), skin rash (10%), hepatitis (15%), endocrine dysfunction (5%), pneumonitis (4%), and inflammatory arthritis (6%); up to 20% of those treated with single agent anti-PD1/PDL1 are similarly affected. Resembling diverse “spontaneous” immune-mediated inflammatory diseases (IMIDs), the toxicities can be life altering. For example, a vitiligo-like depigmenting rash may alter physical appearance permanently, and endocrine dysfunction including hypophysitis or thyroiditis may necessitate lifelong medication and/or disrupt fertility. Some toxicities may be fatal.

Permanent discontinuation of therapy due to toxicity is reported in 5% of trial patients treated with anti-PD1 antibodies [4] and 20% treated with combination therapy, though real-world estimates are as high as 49.9–58.8% and 59.2%, respectively [5]. Most IrAEs occur within 3–14 weeks of CPI treatment, though there are reports of some presenting months to years following cessation of CPI therapy. Neither does a traditional ‘dose-response’ relationship appear to apply, with some patients experiencing severe toxicity after a single dose and others developing none despite years of therapy and profound clinical cancer responses. A link between IrAE incidence and improved cancer response has been demonstrated though positive cancer response is not guaranteed, and IrAEs may complicate assessments of cancer outcomes [6]. Indeed, many IrAEs are managed with early corticosteroid therapy for symptom control, presenting concerns regarding ongoing CPI efficacy, and IrAEs may persist well beyond treatment cessation in some cases.

Despite the use of CPIs for several years out with clinical trials, the pathogenesis of IrAEs remains poorly understood, but evidence for induced dysregulation of systemic adaptive immunity has grown [7]. For example, diversification of the T cell repertoire is a demonstrable consequence of anti-CTLA-4 treatment, with more extensive T cell receptor (TCR) Vβ CDR3 clonotype expansion linked to an increased likelihood of IrAEs in general – potentially mirroring observations in “spontaneous” IMIDs. Moreover, CD8 + rich T cell infiltrates have been observed in tissue from dermatological, gastrointestinal and synovial biopsies from IrAE-affected tissue [8–14]. Finally, anti-CTLA-4/PD-1 combination therapy led to relative expansion and clonal diversification of a normally rare, CD21^lo^ B cell population thought to represent long-lived plasma cell precursors, amongst melanoma patients who developed IrAEs. There is growing evidence of a link between the gastrointestinal microbiome (bacteria colonising the gut) prior to commencement of therapy and the subsequent development of IrAEs, with broader diversity of bacteria more likely to be present in the gastrointestinal tract of patients who respond clinically with improvement of their cancer, and particular bacterial species associated with clinical response or risk of colitis development [15–19].

The over-arching hypothesis of the Monitoring immunE DysregulAtion foLLowing Immune checkpOint-inhibitioN (MEDALLION) study is that a continuum of “latent autoreactivity” exists within the general population, and immune and/or microbiome perturbation as a result of CPI therapy lowers the threshold above which a transition to IrAE occurs (Fig. 1). The key biological question we are addressing is how known pathways of immune dysregulation trigger the transition from immune homeostasis to pathology in CPI recipients. In particular, we have demonstrated that interleukin-6 (IL-6) drives signal transduction and activator of transcription-3 (STAT3)-mediated CD4 + T cell activation during the earliest stages of rheumatoid arthritis (RA), a common IMID, and discriminates patients destined to develop RA from those who will develop alternative forms of inflammatory arthritis [20, 21]. “Pre-exposure” of human naïve CD4 + T cells to levels of IL-6 circulating in early RA enhances both their proliferation and activation following subsequent TCR stimulation, suggesting a mechanism by which immune dysregulation may be promoted in early disease [22]. In addition, STAT3 pathway activation has been associated with other IMIDs, such as inflammatory bowel disease [23, 24] and experimental autoimmune encephalomyelitis, an animal model of multiple sclerosis [25]. Whether similar mechanism(s) underlie IrAE development remains to be explored – acknowledging a diversity of plausible alternatives.

**Fig. 1 Fig1:**
[figure not shown]
Spontaneous immune mediated disease and MEDALLION study hypothesis. Established immune-mediated diseases are well-studied, and their risk factors are increasingly understood in the general population (left panel). In cancer patients, we hypothesise that checkpoint blockade actively “lowers the threshold” at which immune tolerance is lost, permitting systematic monitoring of the events that trigger clinically manifest disease (right panel). The MEDALLION cohort represents a human “model” of incipient immune dysregulation within which we will test this hypothesis.)

## Methods

The current version of the study protocol and associated documentation is available as an Online Supplementary File.

### Study objectives

The study’s primary objective is to establish a clinically well-characterised and immune-phenotyped inception cohort of patients with cancer commenced on immune CPI therapy, thereby enabling the study of immune dysregulation that precedes IrAE development. In order to interrogate mechanisms of IrAE development we will focus on a range of biological measurements at baseline and during therapy, forming the basis of secondary and exploratory objectives. These will include the frequency and activation status of peripheral blood mononuclear cell (PBMC) subsets determined using multi-parameter flow cytometry, the gut and skin microbiome composition, serum cytokine mediators and, where possible, cellular composition of affected tissue.

The secondary objective of the study is to determine whether STAT3 phosphorylation (pSTAT3) in circulating CD4 + T cells of CPI recipients predicts IrAE development at baseline and/or following initiation of treatment.

The exploratory objectives of the study are:

(i)to determine whether baseline and/or dynamic changes in microbiome composition in the skin or gut precede IrAE development in CPI recipients.(ii)to identify immune cellular phenotypes whose dynamic frequency amongst CPI recipients predicts IrAE development.(iii)amongst CPI recipients who develop clinically significant colitis and/or skin dermatoses as adverse reaction(s) to treatment, to characterise immune infiltrates of lesional *versus* non-lesional tissue.(iv)to determine whether circulating cytokine profiles of CPI recipients predicts IrAE development at baseline and/or following initiation of treatment.

### Study design

MEDALLION is a single centre, prospective, longitudinal observational cohort study undertaken from the Northern Centre for Cancer Care, Newcastle upon Tyne, UK. All enrolled participants will receive treatment with combination or single agent CPI therapy routinely as standard care, remaining under study follow up for up to 10 months following CPI commencement or until they develop a “significant IrAE” (SirAE) defined according to pre-determined criteria specific to the affected tissue/organ system - whichever is sooner. In keeping with European Society for Medical Oncology (ESMO) practice guidelines, MEDALLION study-specific SirAE definitions generally align with CTCAE Grade 3, but are modified to reflect the significant impact of certain grade 2 IrAEs on quality of life, for example where warranting treatment with corticosteroids; they are summarised in Table 1.

**Table 1 Tab1:** Grades 2 and 3 IrAE definitions align with ESMO criteria [3]

Organ system(s)	MEDALLION definition of SirAE
Skin	Any grade 3 IrAE or above *or* CTCAE grade *≥* 2 IrAE, warranting topical/systemic steroids and/or (in guidance with consulting dermatologist) warranting diagnostic skin biopsy. *or* Physician-diagnosed new onset vitiligo
Gastrointestinal tract	Any grade 3 IrAE or above *or* Diarrhoea, CTCAE grade *≥* 2 persisting *≥* 3 days, warranting steroid treatment and/or endoscopically/histologically confirmed colitis. (Severity grade 2 is 4–6 liquid stools per day over baseline, or abdominal pain or nausea or nocturnal episodes) *or* CTCAE grade *≥* 2 hepatitis warranting steroids
Endocrine	Any grade 3 IrAE or above *or* Symptomatic autoimmune thyroid disease confirmed biochemically *or* Hypophysitis confirmed biochemically and/or radiologically
Musculoskeletal	Any grade 3 IrAE or above *or* Objectively observed inflammatory arthritis
All other	Any grade 3 IrAE or above

### Study population

The MEDALLION study aims to recruit approximately 70 patients treated with CPIs. Accounting for withdrawals this should provide approximately 66 patients completing the study as shown in Fig. 2. The literature suggests that ~ 50% of patients on combination, and ~ 15% of those on single-agent immunotherapy will experience IrAEs of CTCAE *≥* grade 3 severity, and we anticipate a conservative 1:2 ratio of combination: single-agent recipients in our cohort. Hence, incorporating a 5% drop-out rate, approximately 21/66 patients in our study will experience SirAEs.

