#### Sample size justification

Observations made in a separate study, BIOFLARE [26], on pSTAT3 expression in a subset of circulating CD4 + T cells of RA patients in remission who develop disease flare following treatment cessation *versus* those who do not, were used as a basis for sample size calculation. Assuming CPI recipients with and without SirAEs will display a difference of similar magnitude in CD4 + T cell pSTAT3, enrolment of 66 participants with complete datasets will afford MEDALLION 80% power to detect a difference of ~ 24% between groups at alpha 0.05 (*pilot data used currently in preparation for publication; personal communication, [name] and [name]*). However, the longitudinal nature of our study is an important aspect, as it will allow taking account of the exact time the IrAEs occur. There are very few relevant similar datasets but one recent report found in a Swiss population three immune-related predictors of IrAEs in melanoma patients treated with CPIs: CXCL10, IL-10 and regulatory T cell (Treg) levels with hazards ratios of 12.6, 4.0 and 3.4, respecitvely [27]. Detecting effect sizes broadly similar to these with power 80% at significance level 0.05 requires a minimum of 21 events. Based on the anticipated 32% participants experiencing SirAEs, recruitment and following up of the aforementioned 66 patients will be sufficient for such analyses.

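### The 21/66 expected events do not follow from the rates and regimen mix stated for them, which give 17.6 (26.7%), and 21 is also the stated minimum for 80% power

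*Protocol article*

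**What the plan says.** The Study population section of the protocol article gives two event rates: "The literature suggests that ~ 50% of patients on combination, and ~ 15% of those on single-agent immunotherapy will experience IrAEs" of CTCAE grade 3 or above. It adds a regimen mix: "we anticipate a conservative 1:2 ratio of combination: single-agent recipients in our cohort". It plans about 70 recruits to leave about 66 completers, and concludes: "Hence, incorporating a 5% drop-out rate, approximately 21/66 patients in our study will experience SirAEs".

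The Sample size justification uses this count for the time-to-event analysis. Detecting effects broadly similar to published hazard ratios of 12.6, 4.0 and 3.4 with 80% power at the 0.05 level "requires a minimum of 21 events. Based on the anticipated 32% participants experiencing SirAEs", 66 patients are called sufficient.

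Three other places bear on the figure:
- The Background gives different rates for the same severity: around 55% on combination therapy, and "up to 20% of those treated with single agent anti-PD1/PDL1 are similarly affected".
- The Methods part of the Abstract says: "It is conservatively anticipated that one third of enrolled patients will experience a" SirAE.
- Study design (Table 1) and the Discussion define SirAE more widely than grade 3, adding certain grade 2 events.

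**The concern.** The Study population section presents 21/66 as the consequence of the rates and mix just before it, yet those inputs give a clearly smaller number. The gap matters because the expected count and the required minimum are the same number, 21. An expected count below 21 would remove the stated basis for calling 66 patients sufficient. A reader also cannot tell which set of literature rates the plan relies on, or whether grade 2 events were counted.

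**Working it through.** **Inputs.** Combination 50%, single agent 15%, mix 1:2 (22 and 44 of 66), drop-out 5%, 70 recruited and 66 completing (Study population). Combination 55% and single agent up to 20% (Background). Hazard ratios 12.6, 4.0 and 3.4, 80% power, alpha 0.05, minimum 21 events (Sample size justification).

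**Step 1: drop-out.** 66 / 0.95 = 69.5, rounded up to 70. This step is correct, and the 5% is spent in going from 70 to 66.

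**Step 2: expected events from the Study population inputs.** The rate is (1/3)(0.50) + (2/3)(0.15) = 0.2667.
- 66 patients: 22 × 0.50 + 44 × 0.15 = 17.6
- All 70 recruited: 18.7
- 66 / 0.95 = 69.5: 18.5
- 70 × 0.95 = 66.5: 17.7
- Drop-out taken off a second time, 66 × 0.95 = 62.7: 16.7

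The range is 16.7 to 18.7. The stated figure is 21/66 = 31.8%. The expected count on 66 is 3.4 below it (3.4/21 = 16%).

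**Step 3: what does give about 21.** The Background rates do: 22 × 0.55 + 44 × 0.20 = 20.9 (31.7%). So would a 1:1 mix with the Study population rates (66 × 0.325 = 21.45), or 50% and 20% applied to all 70 (70 × 0.30 = 21.0). The article does not say which was used. The Background rates are the only complete set it prints that reproduces both 21/66 and 32%. Its 20% is worded as an upper limit.

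**Step 4: reproduce the 21-event minimum.** The article states neither the formula, the sidedness nor the marker split. The Schoenfeld formula with a two-sided 0.05 test and a 50:50 marker reproduces it:

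events = (1.96 + 0.8416)² / (0.25 × (ln HR)²)

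- HR 3.4: 7.849 / (0.25 × 1.2238²) = 20.96, rounded up to 21
- HR 4.0: 17
- HR 12.6: 5

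The minimum is therefore set by the smallest hazard ratio. Other assumptions move it for HR 3.4: 17 if one-sided, 24 with a one-third split, 27 by Freedman's formula.

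**Step 5: power at 17.6 events, same assumptions.** Power = Φ(√(0.25 × 17.6) × ln HR − 1.96), with √4.4 = 2.098.

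| HR | Power at 21 events | Power at 17.6 events |
|---|---|---|
| 3.4 | 80.1% | 72.8% |
| 4.0 | 88.8% | 82.8% |
| 12.6 | >99.9% | >99.9% |

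The hazard ratio detectable with 80% power is exp(2.8016 / 2.098) = 3.80, against 3.40 at 21 events. With the count rounded to 18 it is 3.75.

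**Step 6: distance to 21.** 21 − 17.6 = 3.4 patients, which is 3.4/66 = 5 percentage points, or 3.4/48.4 = 7% of those expected to have no grade 3 or higher event.

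**The case against.** The strongest reply is that 50% and 15% are rates of grade 3 or higher IrAEs, while the endpoint is SirAE. Table 1 also counts, among others, grade 2 skin events needing steroids or a diagnostic biopsy, new vitiligo, grade 2 diarrhoea or hepatitis treated with steroids, symptomatic thyroid disease and observed arthritis. On that view 17.6 is nearer a floor than an expectation, and 3.4 further patients would close the gap. This stands as a limit on the conclusion. It does not rescue the sum, because the article derives 21 from the grade 3 rates alone and mentions no allowance for grade 2 events. The requirement that a SirAE be definitely or probably related to treatment could also pull the count down somewhat; neither effect is quantified.

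A reader might infer that the study will miss its 21-event minimum and lose its 80% power. The documents do not support that:
- A shortfall in SirAEs is not shown, for the reason just given. The same applies to calling the Abstract's one third over-optimistic, since that compares a SirAE rate with a grade 3 rate.
- The power loss applies only to HR 3.4. The claim is worded for effects broadly similar to three hazard ratios, and the other two stay above 80%.
- The separate claim of 80% power for a difference of about 24% in pSTAT3 cannot be recomputed, since neither a standard deviation nor a group split is given. Purely as an illustration, if it had been set at a 21:45 split, an 18:48 split would give about 76%.

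It is also fair to say that this is an observational cohort whose primary aim is to establish the cohort and generate pilot data. No treatment, endpoint or recruitment target depends on the correction.

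**Conclusion.** The stated derivation is wrong as written. The rates and mix in the Study population section give 17.6 events among 66 (26.7%), so neither 21/66 there nor 32% in the Sample size justification follows. The printed figures agree with the Background's rates, so the two sections conflict.

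On the Study population inputs alone, power for HR 3.4 is about 73% instead of 80%, and the hazard ratio detectable with 80% power is about 3.8. These power figures assume the Schoenfeld formula, a two-sided 0.05 test and a balanced marker, which together reproduce the plan's 21. The event arithmetic needs no assumption beyond the stated inputs.

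Whether SirAEs will number fewer than 21 is not established. This should be fixed, because a number the sample size rests on does not follow from its stated source; it is not a threat to the design.

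**What to change.** 1. Reconcile the rates in the Background (55%, up to 20%) with those in the Study population section (50%, 15%), and use one set.
2. State an explicit SirAE rate for each regimen, with the assumed contribution of qualifying grade 2 events and its source, and show the sum for 22 and 44 patients.
3. Restate the expected number of events, and the power for each cited hazard ratio, consistently in the Abstract, Study population and Sample size justification. Name the formula, sidedness and marker split.
4. If no grade 2 contribution can be justified, state about 18 events (27%) as the count the sample size rests on, labelled as derived from grade 3 or higher rates, with 80% power for a hazard ratio of about 3.8 and about 73% for 3.4. It should not be presented as a SirAE expectation without that label, because the two endpoints differ.

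The cost is wording only, with no added patients. The one downside is a slightly less favourable power statement if the lower count is kept.

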**Fig. 2 Fig2:**
[figure not shown]
MEDALLION enrolment plan and design. Clinical assessments will take place at all patient visits, planned to coincide with routine hospital visits, and red arrows indicate time points at which 53 ml research bloods will be drawn (providing irAE has not occurred); additional research bloods +/- biopsy will be obtained at the time of incident SirAE)

## Eligibility criteria

### Inclusion criteria

Male or female patient *≥* 18 years of age.Confirmed diagnosis of malignant melanoma, NSCLC or mesothelioma.Shared decision by oncologist and patient to proceed with CPI treatment, either with the combination of ipilimumab and nivolumab, or with single-agent nivolumab, pembrolizumab or atezolizumab as standard of care.Patient is judged as being capable of understanding the information sheet and of giving informed consent according to the Mental Capacity Act 2005.Written informed consent to participate in the study.

### Exclusion criteria

Known pre-existing autoimmune or immune-mediated inflammatory disease requiring immunomodulatory treatment, including (but not limited to) inflammatory bowel disease (Crohn’s disease, ulcerative colitis) autoimmune endocrinopathy or hepatitis, vitiligo and inflammatory arthritis.Received enteral or parenteral steroids within past month (topical, inhaled or intranasal permitted).Previous treatment with CPI therapy.Vaccination within the past 4 weeks, except COVID-19 vaccination permitted.Known chronic infection.Current pregnancy, or pregnancy planned within next 6 months.Inability to provide informed consent and/or undergo any of the procedures mandated by the study.

